## Introduction

Across the globe, societies are struggling to meet the needs of an aging population [1-5]. The increasing prevalence of dementia [6-8] and comorbid chronic conditions [9,10] lead to complex care needs [9,10] and to greater family or friend caregiver burden [11-14] (ie, “the extent to which caregivers perceive that caregiving has had an adverse effect on their emotional, social, financial, physical, and spiritual functioning” [15]). In response, health systems provide a range of ongoing care and supports to older adults and their caregivers—in Canada commonly referred to as continuing care [2,16]. Continuing care can be provided in an older adult’s private home, in the community (eg, an adult day program), or in a variety of congregate care settings including independent living, retirement homes, supportive or assisted living, or nursing homes (NHs) [17,18]. Governments have identified NHs as a major driver of public continuing care costs [17,19-21]. To mitigate pressures on public continuing care systems, and to meet aging in place preferences of older adults and their caregivers [22-24], reforms have implemented aging in place strategies. These strategies largely include (1) reserving NH care to those with the most complex care needs, and (2) improving access to an array of publicly funded continuing care options in the community [2].

Adult day programming is such a continuing care option to support aging in place [25-32]. Older adults in need of continuing care usually attend these programs for parts of the day, returning to their homes overnight (but overnight services are provided by some day programs). As this literature illustrates [25-32], the number of days a person attends a day program can vary widely, depending on the program and health jurisdiction, from a couple of days or month to daily attendance. The amount of time an individual attends also varies from a few hours or day to all day, or sometimes during nights, and so do admission criteria, supports and services offered, and funding models.

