### Sample Size Calculation

The yearly average number of completed RAI-HC assessments is ~20,000-30,000 in Alberta, ~34,000-39,000 in British Columbia, and ~10,000 in Manitoba [67]. About 50% of those assessed receive a reassessment within 12 months and another 10%-30% receive a reassessment after >15 months [68]. There are 89 publicly subsidized day programs in Alberta (~3300 spaces per day), 95 in British Columbia (~1500 spaces per day), and 70 in Manitoba (~1000 spaces per day) for a total of 254-day programs with 5800 spaces on any given day. Some day program users do not attend daily, but only 1 or a few days per week, so the number of unique attendees exceeds the number of spaces per day. This corresponds to >20,000 attendees per year (>200,000 within the study period), each with multiple assessments. Our study sample size will be large enough to detect small effects sizes. With Cox proportional hazards models, adjusted for covariates explaining an assumed 25% of effect variance (a=.05; power=0.8) [69], we require a total sample of 1327 participants to detect a hazard ratio for admissions to care homes of 0.6 (as can be expected based on a similar Canadian study [42]) in favor of day program attendees. Similarly, Kelly [43] was able to detect significantly fewer emergency department visits and hospital admissions per day among 812 day program attendees compared with 812 propensity score matched to nonattendees. Our expected sample size will be considerably larger than for those previous studies, allowing for complex statistical modeling.

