#### Objective 3: Assess Effects of Day Programs

To create a propensity score, we will run a logistic regression for each province with day program attendance or nonattendance as the dependent variable and adding matching covariates. We will use one-to-one matching (1 matched nonattendee for every attendee) [78]. We will use matching without replacement [85] and apply an optimal caliper matching algorithm [86]. As per best practice recommendations [87], we will use a caliper width of 0.2 of the SD of the propensity score’s logit. If this matching approach does not allow us to achieve a sufficient sample size, we will use propensity score quintiles for matching.

We will compare sample characteristics and study outcomes between attendees and nonattendees in every year and province, using bivariate statistical tests (eg, chi-square test or Fisher exact test for categorical variables, *t* tests, or ANOVAs for continuous variables, and their nonparametric equivalents if variables violate statistical assumptions). To assess the effect of day program exposure on time to care home admission, we will specify a multilevel time-to-event model with a health region–level random effect [88]. Health systems in each of the 3 provinces are divided into 5 health regions [89-91], and regional policies may cause clustering effects that our models must account for. Each model will include day program use or nonuse class as independent variable and will be adjusted for time-varying variables. These will include matching variables, if appropriate (ie, in case of group differences in matching variables over time or due to missing data) [80-82] and, if needed, additional covariates (eg, demographics, social determinants, medical or functional conditions, and non–day program community care). Covariates that differ between attendees and nonattendees with a *P* value of ≤.15 in the bivariate analyses will be considered for inclusion. We will add covariates stepwise, one-by-one, and remove those that cause collinearity issues or decrease model fit. As in objective 2, we will pool provincial effects statistically, using random-effects mixed regression models.

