Using GEEs and a similar approach as for the time-to-event models (including separate models in each province and statistical pooling of their effects), we will assess whether the other study outcomes differ by day program use or nonuse pattern. Models will include each study outcome of interest as a dependent variable, day program use or nonuse class and time of assessment as independent variables, and similar covariates (using the same stepwise approach) as the time-to-event models. Models will also include a random term to account for repeated measures within individuals. The choice of a link function will be informed by the nature of the variable and theoretical and empirical considerations. For example, the number of hospital, emergency department, or physician visits has been shown to follow a zero-inflated negative binomial distribution, sometimes requiring an offset for the natural logarithm of person-time [92]. For continuous outcomes (eg, days spent in hospitals), we will use an identity link function, and for dichotomous outcomes (eg, presence or absence of depressive symptoms), we will use a logit link function. All models will apply multiple imputation in case of missing data, which we expect to be small based on our previous work with the administrative health care data sources used in this study.

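### The Objective 3 models allow for dependence by health region and person but not by day program; if outcomes correlate within programs, provincial standard errors for use versus nonuse are too small

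*Protocol article*

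**What the plan says.** The time-to-event model has one clustering term: "we will specify a multilevel time-to-event model with a health region–level random effect" (Objective 3). The reason given is that policies differ between the five health regions of each province. The GEEs for the other outcomes follow a similar approach, and "Models will also include a random term to account for repeated measures within individuals". Neither paragraph mentions the day program as a level.

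The Sample Size Calculation counts 89, 95 and 70 programs in the three provinces, "for a total of 254-day programs with 5800 spaces on any given day". The Introduction says that attendance varies between programs and "so do admission criteria, supports and services offered, and funding models". The Limitations section says that program characteristics are not in the available data. Controls come from matching: "We will use one-to-one matching (1 matched nonattendee for every attendee)". Models are fitted in each province and the effects are then pooled by random effects.

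**The concern.** Day programs are delivered to groups. Attendees of one program share its staff, activities and opening pattern, so their outcomes may be more alike than those of attendees elsewhere. Nonattendees belong to no program, so the comparison is partially nested: program-to-program variation enters on the attendee side only and goes directly into the use-versus-nonuse contrast.

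A region intercept does not remove it. With 70 to 95 programs and five regions per province, a region holds on average 14 to 19 programs (70/5 and 95/5), and attendees and nonattendees share the same intercept. A person-level term handles repeated assessments, not similarity between people. Because program characteristics are unavailable, covariates cannot absorb the variation either.

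At stake is the precision of the provincial estimates for care home admission, service use, decline and mood. More attendees per program do not cure this, because the number of programs is fixed.

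**Working it through.** **The plan's own figure.** The article states "we require a total sample of 1327 participants to detect a hazard ratio for admissions to care homes of 0.6", with 80% power, alpha .05, "adjusted for covariates explaining an assumed 25% of effect variance". The event proportion is not given, so 1327 cannot be fully reproduced. Schoenfeld's formula (two-sided and 1:1 assumed) gives 4 × (1.96 + 0.842)² / (ln 0.6)² = 120.3 events, and 120.3 / (1 − 0.25) = 160.4 events after covariate adjustment. A total of 1327 then implies that 160.4/1327, about 12.1%, are admitted. The figure is plausible and contains no clustering inflation. At that size there would be about 1327/2/254 = 2.6 attendees per program, and clustering hardly matters: type I error 5.1% at ICC 0.01 and 5.5% at 0.05.

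**Inputs at the planned scale**
- Programs: 254 (Sample Size Calculation).
- Attendees: "This corresponds to >20,000 attendees per year (>200,000 within the study period), each with multiple assessments". One year's count gives m = 20,000/254 = 78.7 per program.
- Allocation 1:1, controls unclustered.
- ICC after matching, covariates and region: not in the document. The values 0.01 to 0.05 are assumptions.

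**Formulas.** Attendee design effect DE = 1 + (m − 1) × ICC. Variance ratio of the contrast = (DE + 1)/2. True type I error = 2 × [1 − Φ(1.96/√ratio)].

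| ICC | DE | Variance ratio | SE understated by | Type I error, one province |
|---|---|---|---|---|
| 0 | 1.00 | 1.00 | 1.00 | 5.0% |
| 0.001 | 1.08 | 1.04 | 1.02 | 5.5% |
| 0.01 | 1.78 | 1.39 | 1.18 | 9.6% |
| 0.02 | 2.55 | 1.78 | 1.33 | 14.2% |
| 0.05 | 4.89 | 2.94 | 1.72 | 25.3% |

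As an outer bound, 200,000/254 = 787 attendees per program gives 9.7% at ICC 0.001 and 38% at 0.01. That count may include the same person in several years.

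**Effect of pooling.** Simulation used a linear outcome, 89, 95 and 70 programs of equal size, no program term, and DerSimonian-Laird pooling as one reading of the plan. With 79 attendees per program, the pooled type I error was roughly 6%, 8 to 9% and 12 to 13% at ICC 0.01, 0.02 and 0.05. With 787 per program it was 6.7% at ICC 0.001 and 18% at 0.05. A Hartung-Knapp interval on 2 degrees of freedom held about 5% throughout.

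**Effect of use classes.** The modelled exposure is use or nonuse class. With four classes (assumed), 79/4 is about 20 attendees per program and class. Against an equal number of controls, the one-province error is 6.1%, 7.2% and 10.7% at the same three ICCs. Against the whole control group, four times the class, the ratio becomes (DE + 1/4)/(1 + 1/4) = 1.15, 1.30 and 1.76, and the error 6.8%, 8.6% and 14.0%. After pooling as above, simulation gives about 4.5 to 4.7%, 5.0 to 5.9% and 6.9 to 8.5%.

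**With program-level variance in the analysis**, one-province error in the simulation was 4.8 to 5.3%.

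**The case against.** The strongest reply has five parts.

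- *No ICC is given, and it may be small.* The variation described in the Introduction comes from the wider literature across jurisdictions. Setting and Sample says eligibility in the three provinces follows comparable processes and criteria. This stands. A reader might infer that false positives certainly exceed 5%; the document does not support that, because it depends on a residual ICC above zero that nobody has stated.
- *Pooling absorbs part of the excess.* This also stands. The 9.6 to 25% figures belong to a single province, or to fixed-effect pooling. But provincial models are fitted, and the article plans to present jurisdictional differences in effects, so the provincial standard errors matter in their own right.
- *The approximation is rough.* A linear design effect is carried over to hazard, count and binary models. Some shared influences, such as local care supply, also reach nonattendees nearby and partly cancel. Comparisons between use classes are partly within program, where omitting the term need not understate the error. All of this stands and argues for reading the figures as orders of magnitude.
- *The GEEs may carry the region term.* The similar-approach wording allows it, so one should not infer that they handle person-level dependence only. Region is still not program.
- *The programs may be the whole population.* If inference is limited to exactly these programs, the inflation does not arise. The article does not say so, and its conclusions speak of day programs in general and of extension to other jurisdictions.

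A condensed article may leave variance estimators to a fuller plan. Here, however, the article itself names the clustering levels and says that its models must account for clustering.

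**Conclusion.** The point holds conditionally. The stated dependence structure leaves out the level at which the exposure is delivered, and for any positive residual program ICC the provincial standard errors for use versus nonuse are too small. At about 79 attendees per program and assumed ICCs of 0.01 to 0.05, the understatement is a factor of 1.18 to 1.72, with provincial type I error of about 9.6 to 25%. The pooled error is roughly 6 to 13%, and closer to nominal when attendees are split across use classes. These sizes rest on the assumed ICCs, equal program sizes, unclustered controls, a linear outcome and DerSimonian-Laird pooling.

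Two stronger readings are not supported: that the study's pooled conclusions are known to be anticonservative, and that the sample size of 1327 is wrong on this account. At that size the effect of clustering is trivial.

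**What to change.** Ask each province for the program identifier along with the registry attendance data. The Exposure section lists start and stop dates, days attended and visit durations but no identifier, so availability has to be confirmed.

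- **Where it is available, time-to-event model:** add a program-level random effect that applies to attendees only, with nonattendees as singletons, alongside the region effect.
- **Where it is available, GEEs:** use robust variance clustered by program for attendees and by person for nonattendees. If the matched pairing is to be respected, use two-way clustering by program and matched pair. Taking the matched pair as the cluster for nonattendees alone would conflict with clustering the paired attendee by program.
- **Where it is not available:** report a sensitivity analysis with intervals inflated over an assumed ICC range such as 0.01 to 0.05, or state that inference is conditional on the existing programs.

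Pool the resulting provincial standard errors, and say in the GEE paragraph whether the region term applies there.

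The cost is one more data field, which a province may not hold, a changed model statement in the shared programs, and wider intervals. Matching, outcomes and cohort are untouched.

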Explore patterns of day program use (eg, variations in time to first attendance, monthly hours of attendance, ongoing versus interrupted attendance, and total time of day program exposure), using latent class analyses (LCA), and compare the frequency of each latent use class between provinces and over time.Compare older adults’ demographic, social, and health characteristics (eg, age, sex, physical or cognitive disability, area-based deprivation indices, and caregiver availability or distress) by day program use or nonuse class, province, and time.Assess whether, compared with a propensity score–matched control group of nonattendees, day program attendees enter care homes at later points in time; use emergency, acute, or primary care less frequently; experience less cognitive and physical decline; have better mental health; and have less distressed caregivers. We will assess potential modification of these effects by day program use or nonuse class, age, sex, and social determinants of health (eg, area-based deprivation indices).

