### Study Variables

#### Exposure

Our exposure will be different patterns of day program use or nonuse, based on information from the provincial continuing care registries, documenting the dates a person starts or stops attending a day program, days of attendance, and the duration of each visit. Day program use patterns will be determined, using LCAs (see *Statistical Analyses* section) [71]. We will categorize three continuous variables as low, low-moderate, high-moderate, or high use, using sample distribution quartiles: (1) time between first RAI-HC assessment and first attendance of a day program; (2) average number of hours of day program attendance (ie, total number of hours spent in a day program divided by the number of times attended); and (3) total number of days a person attended a day program. LCAs will also include a categorical variable, indicating whether a person consistently attended a day program or whether there were longer periods (several weeks) of nonattendance. Nonuse will be defined as no day program exposure at any time during a person’s continuing care trajectory.

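### The match balances attendees as a whole, but the outcome models compare each use class with the pooled matched nonattendees, and the planned adjustment may not restore balance by class

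*Protocol article*

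**What the plan says.** In the section on objective 3, the propensity score comes from a "logistic regression for each province with day program attendance or nonattendance as the dependent variable". Matching is without replacement, with "1 matched nonattendee for every attendee" and a caliper of 0.2 SD of the logit. Propensity score quintiles are the fallback if too few matches are found.

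The exposure in the outcome models has more levels. For time to care home admission, "Each model will include day program use or nonuse class as independent variable". For the other outcomes, the GEEs take "day program use or nonuse class and time of assessment as independent variables". The Exposure section makes nonuse one undivided category: "Nonuse will be defined as no day program exposure at any time" during the care trajectory. Among the objectives in the Introduction, the third states: "We will assess potential modification of these effects by day program use or nonuse class", so class-specific effects are a declared aim.

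On adjustment, the objective 3 section says that models are adjusted for time-varying variables. Matching variables are included if appropriate, meaning when groups differ on them over time or data are missing. Further covariates are considered if attendees and nonattendees differ at P≤.15. They are then added stepwise and dropped if they cause collinearity or worsen fit.

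**The concern.** The score and the match target a single contrast, attendees as a whole against their matched nonattendees. The models estimate a set of other contrasts, each use class against all the matched nonattendees together. Balance for the whole is an average over classes, so one class can be frailer than the controls and another fitter while the average shows no difference.

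If that happens on a prognostic variable, a class can appear to enter care homes earlier or later for reasons present before anyone attended. With samples as large as the plan expects, such an artefact would be estimated precisely and could be read as an effect of the pattern of use. The effect that the match does support, ever attending against matched never attending, has no stated term in the outcome models.

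**Working it through.** The plan gives no figure for balance or bias by class, so there is none to reproduce. Its sample size of 1327 does not enter this point.

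**Step 1: what the match secures.** Let d_k be the mean difference on a baseline covariate between class k and the pooled matched nonattendees, and w_k the share of attendees in class k. Matching on attendance aims at Σ w_k·d_k ≈ 0. It does not constrain any single d_k. With two equal classes, d = +0.2 and −0.2 SD give 0.5×0.2 − 0.5×0.2 = 0.

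**Step 2: whether the planned screen would see it.** The P≤.15 screen tests attendee against nonattendee, which is the weighted sum in Step 1. The imbalances in the example cancel there, so the covariate gives no signal. The condition for entering matching variables (group differences over time or missing data) does not mention use class. Values entered as time-varying may themselves be affected by attendance, so they do not replace values at the index date.

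**Step 3: size before adjustment.** The inputs are assumptions, because the article gives neither the strength of the link between covariates and class nor prognostic effects. With no true effect, the false class-versus-nonuse hazard ratio is about exp(±ln(HR per SD) × shift).

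| HR per SD | Shift (SD) | False HR, class vs nonuse |
|---|---|---|
| 1.3 | 0.1 | exp(±0.262×0.1) = 1.03 or 0.97 |
| 1.5 | 0.2 | exp(±0.405×0.2) = 1.08 or 0.92 |
| 2.0 | 0.3 | exp(±0.693×0.3) = 1.23 or 0.81 |

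**Step 4: simulation with no true effect.** The set-up, again assumed, was:
- 60,000 people, about 8% of them attending.
- Two covariates, X1 and X2, drive attendance. X1 also carries a log hazard ratio of 0.4 per SD.
- Two use classes, with log-odds slope g of class on X1.
- 1:1 nearest-neighbour matching within 0.2 SD of the logit. It was greedy, where the plan specifies optimal matching.
- One run per value of g.

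| g | Ever/never SMD on X1 (P) | Class SMDs on X1 vs pooled controls | Class HRs, unadjusted | Class HRs, adjusted for X1 and X2 |
|---|---|---|---|---|
| 0 | −0.01 (.53) | −0.03, 0.00 | 1.05, 1.00 | 1.06, 1.00 |
| 0.5 | −0.01 (.61) | +0.24, −0.27 | 1.12, 0.90 | 1.03, 1.01 |
| 1.0 | 0.01 (.58) | +0.45, −0.42 | 1.16, 0.84 | 0.98, 0.99 |

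SMD is the standardized mean difference. The g = 0 row shows that departures of about 0.05 are chance in a single run. With g above 0, the ever/never P values are far above .15 while the classes are clearly unbalanced. Always adjusting for both matching covariates brings the class hazard ratios back to 0.98 to 1.03.

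**Step 5: whether each class's own matches suffice.** In the same runs with g above 0, comparing each class with its own matched controls left X1 differences of 0.10 to 0.26 in size, with opposite differences on X2. Matched pairs share a score, not covariate values, so own-match comparison helps only in part.

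**The case against.** The strongest reply is that the plan does not rely on matching alone. It allows adjustment for matching variables, demographics, social determinants, medical or functional conditions and other community care, in both the time-to-event models and the GEEs. Step 4 shows that full adjustment repairs the baseline imbalance. This stands in part: adjustment is available, but whether the right variables enter depends on triggers tied to the contrast already balanced, and their values are not fixed at the index date.

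Second, it is not known that classes differ at baseline. This stands. A reader might infer that objective 2 presupposes such differences, but it only plans to assess whether characteristics are associated with use pattern. If they are not, this bias is nil.

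Third, entering class levels against nonuse is an ordinary way to show effects by pattern, an overall effect can be averaged from the class coefficients, and attendees and nonattendees are compared bivariately. This also largely stands. A reader might infer that modification by class cannot be estimated because nonattendees have only one class value. The article specifies no interaction term, so that is a matter of wording.

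The reply that a condensed article leaves such details to the analysis plan does not dispose of the point. The article itself states both the binary score and the multi-level exposure, and the two do not fit.

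**Conclusion.** The point holds as a mismatch between what is matched and what is modelled, with a safeguard that may not act. Its size rests on assumptions: about 1.03 to 1.23, or the inverse, for a class-versus-nonuse hazard ratio before adjustment, and nothing if baseline covariates do not predict class.

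Four stronger readings are not supported:
- A reader might infer that classes are compared with every nonattendee in the cohort. Objective 3 uses the matched control group.
- A reader might infer that most controls of a given class belong to other classes' pairs. That depends on the number and sizes of classes, which are not yet known.
- A reader might take the ratio between two oppositely shifted classes (1.05 to 1.52 on the same inputs) as the bias. It doubles the log bias of the planned class-versus-nonuse contrast.
- A reader might infer that objective 3 as a whole is compromised. The ever-versus-never contrast remains protected for the matched covariates.

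Separately, classes are defined by attendance after the index date. Nothing here addresses that.

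**What to change.** 1. In every model with class as exposure, always adjust for the index-date values of all matching covariates, whatever the P≤.15 screen or the stepwise fit shows. For nonattendees, these are the values from the assessment used for matching.
2. Report standardized differences for each use class against its comparison group, in each province.
3. Fit attendance (ever versus matched never) as an explicit term and make it the main objective 3 effect. Report class-specific contrasts separately.
4. Where pairs exist, optionally give each control the class of its matched attendee, so that each class can be set against its own matches. Use this together with the adjustment in item 1, not instead of it. It is not available under the quintile fallback, which leaves no pairs.
5. Reword the third objective in the Introduction so that modification by use or nonuse class means these class-specific contrasts.

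The cost is a few sentences and slightly more work in the shared programs. If own-match contrasts are used, class-specific intervals will be somewhat wider.

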Our first set of matching covariates will be RAI-HC variables used by health systems to determine day program eligibility [60,65,66]: physical functioning (ADLh Scale), cognition (CPS), behavioral symptoms (Aggressive Behavior Scale [79]), bladder or bowel continence (items I1, I3), availability of a caregiver (item G1e), and caregiver distress (items G2a-c). This will ensure that control participants are potentially eligible to a day program. Possible reasons for nonattendance include the lack of day program spaces, preference not to attend, inability to afford the required copayments, or not receiving a day program referral. Our experts assure us that the pool of potential matches far exceeds that of attendees, supporting the feasibility of this study and underscoring the lack of day program spaces. This approach excludes individuals whose care needs are either too low or too severe for day program eligibility, but it minimizes confounding by the matched variables and ensures comparable groups at baseline [80-82]. Finally, we will include a second set of matching covariates: health and social characteristics identified in objective 2 by which attendees and potentially eligible nonattendees differ and that overlap sufficiently between attendees and nonattendees (eg, age, sex, type or duration of publicly funded community care received before the matching index date, and deprivation indices).

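### The objective 3 effect models adjust for post-index function and cognition, which are also study outcomes, so the estimates may not be the total effect of attendance

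*Protocol article*

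**What the plan says.** All references are to the protocol article.

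- **Adjustment (Objective 3: Assess Effects of Day Programs).** For time to care home admission: "Each model will include day program use or nonuse class as independent variable and will be adjusted for time-varying variables". Matching variables belong to this set where suitable, which the article spells out as "in case of group differences in matching variables over time or due to missing data". Functional conditions and other community care may be added if needed.
- **Selection (same section).** Attendees and nonattendees are compared in each year and province. Covariates that differ at P≤.15 become candidates. Then: "We will add covariates stepwise, one-by-one, and remove those that cause collinearity issues or decrease model fit".
- **Other outcomes (same section).** The GEE models use similar covariates and the same stepwise approach.
- **Matching variables (Propensity Score–Matching Variables).** The first set is "physical functioning (ADLh Scale), cognition (CPS), behavioral symptoms (Aggressive Behavior Scale [79]), bladder or bowel continence", followed by caregiver availability and caregiver distress. Attendees' values come from the eligibility assessment, which is the index date.
- **Outcomes.** The third objective in the Introduction asks whether attendees "experience less cognitive and physical decline; have better mental health; and have less distressed caregivers". Study Outcomes measures physical and cognitive decline on the same ADL Hierarchy (ADLh) and Cognitive Performance Scale (CPS) used for matching.
- **Exposure (Exposure).** Use classes are latent classes built from time to first attendance, hours per visit, total days attended and interruptions.

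**The concern.** Matching is meant to make the groups alike on ADLh, CPS and caregiver distress at the index date. If they later diverge on these variables, one explanation is the effect that objective 3 sets out to find. The plan names divergence over time as a reason to put the same variables back into the model. Putting post-index values into an ordinary Cox or GEE model blocks whatever part of the effect runs through them. If unmeasured factors drive both later function and care home admission, it can also open a collider path.

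At stake is the meaning of the main result. A reader will take the hazard ratio as the effect of attending on care home admission, but the model may deliver only the part that does not pass through function, cognition or caregiver strain. Selecting covariates by P value within each province adds a second problem: the provincial coefficients that are pooled may be adjusted for different things.

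**Working it through.** **1. Do the same variables appear in both roles?**

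| Construct | Matched at index | Outcome in the third objective | Outcome in Study Outcomes |
|---|---|---|---|
| Physical function (ADLh) | yes | yes | yes |
| Cognition (CPS) | yes | yes | yes |
| Caregiver distress | yes | yes | not listed |

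ADLh and CPS carry the point without caregiver distress.

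**2. The plan's effect size.** Sample Size Calculation gives a hazard ratio (HR) of 0.6, alpha .05, power 0.8, a covariate share of 25% and a total of 1327. With two-sided alpha (sidedness is not stated) and 1:1 groups, the Schoenfeld formula gives (1.960 + 0.842)² / (0.25 × (ln 0.6)²) = 120.3 events, and 120.3 / 0.75 = 160.4. No event probability is stated, so 1327 can be neither reproduced nor refuted; it implies 160.4 / 1327 = 12.1%. The point does not rest on this figure. Only the HR of 0.6 is carried forward.

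**3. Illustration of attenuation.** The documents give no mediated share m, so it is assumed over a range. The HR targeted after adjusting for the mediators is 0.6^(1 − m):

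- m = 25%: 0.6^0.75 = 0.68
- m = 50%: 0.6^0.50 = 0.77
- m = 75%: 0.6^0.25 = 0.88

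A small Cox simulation agrees in pattern (three runs of 4000 people, mediator updated yearly, total HR set near 0.6):

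| Assumed mediated share | HR, baseline value adjusted | HR, time-varying value adjusted |
|---|---|---|
| 0% | 0.614 | 0.615 |
| 25% | 0.580 | 0.659 |
| 50% | 0.561 | 0.715 |
| 75% | 0.603 | 0.896 |

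With three runs per row, the spread in the middle column is mostly Monte Carlo error. The two adjustments part only when attendance affects the variable.

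**4. What P≤.15 selects.** For two equal groups of n, the standardized difference that just reaches two-sided P = .15 is 1.44 × √(2/n). The article expects more than 20,000 attendees a year over three provinces. An equal split (assumed) gives 20,000 / 3 ≈ 6,700, or about 7,000 per test; 2,000 stands for a smaller province or matched subset (assumed).

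- n = 7,000: 1.44 × √(2/7,000) = 0.024
- n = 2,000: 1.44 × √(2/2,000) = 0.046

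Both are far below the 0.1 commonly used to judge balance.

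**The case against.** **The adjustment is conditional.** Matching variables enter only where suitable, further covariates only if needed, and those passing P≤.15 are merely considered. Missing data is a second trigger and is not a program effect. This stands as a limit on certainty. It does not remove the problem, because divergence over time is itself a named reason to adjust and nothing restricts the adjustment to index-date values.

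**The yearly comparisons may be by calendar year.** That reading is possible. If they used index-date values only, the screen would not pick up program effects. The rule on differences over time and the time-varying adjustment would remain.

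**Later function may be a confounder.** This is the strongest point. The use classes are built from attendance after index, and eligibility depends on function, continence and behavior, so decline may shape class membership as well as admission. Index-date adjustment alone does not deal with that. Ordinary time-varying regression does not solve it either, since it still blocks the mediated path.

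**Provincial analyses are coordinated.** Study Design promises shared protocols and programs. That helps, but stepwise selection run separately in each province can still end in different covariate sets.

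**Stronger readings that the article does not support:**

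- A reader might infer that baseline depression and earlier emergency, hospital and physician use are left out. The covariate lists are open, given by example, and partly await objective 2, so no omission is shown.
- A reader might infer that each outcome model adjusts for its own construct. The GEE covariates are called similar, not identical.
- A reader might put the all-province 20,000 into the screening formula and get 0.014. The tests are by year and province, so that n is too large.

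**Conclusion.** The point holds as a fault in a stated rule, not as a gap that an unseen analysis plan might fill. Followed as written, the plan allows, and tends to bring about, ordinary adjustment for post-index ADLh and CPS, and for caregiver distress on the wording of the objective, although day programs are hypothesized to change them.

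That part of the effect is certainly adjusted away is more than the documents show. They give no mediated share, and collider paths could move the estimate either way. The HRs of 0.68, 0.77 and 0.88 illustrate assumed shares of 25%, 50% and 75% of a total effect of 0.60; they are not predictions. The screening thresholds of 0.024 and 0.046 rest on assumed group sizes, but the conclusion that trivial differences qualify is not sensitive to them.

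**What to change.** 1. Take the main attendee versus nonattendee estimate for each outcome from models adjusted only for index-date covariates, using one prespecified list in all three provinces. Do not adjust these models for post-index ADLh, CPS or caregiver distress.
2. Delete the P≤.15 screen and the stepwise rule. Judge balance after matching by standardized differences. Where imbalance remains or data are missing, adjust for the index-date value, with the multiple imputation already planned.
3. For comparisons between use classes, handle time-varying confounding with a marginal structural model or a similar method, labeled separately from the main estimate. Do not use ordinary time-varying adjustment for this.

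The cost is a little more analysis work. The sources for these covariates are already in the planned linkage under Data Sources. The main estimate becomes a total effect and does not address time-varying confounding of continued attendance; the separate class analysis is there for that.
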